### Sample size

The sample size calculation was based on total SPADI score at 12 weeks, powered to detect a minimal clinically important difference of 8 points between groups.^10^ Assuming an SD of 30 (the upper 80% confidence limit from our pilot study)^6^ at 90% power and significance level 5%, and using an independent t-test, results in 297 participants being needed per group (594 in total). However, using Analysis of Covariance (ANCOVA) (primary analysis), adjusting for the baseline SPADI score, where correlation (r) between baseline and 12 weeks=0.2 (data from pilot RaCeR RCT), the sample size was adjusted by (1-r2) plus one extra participant per group to 574 in total.^11^ In addition, adjusting for 10% non-response of SPADI questionnaire at 12 weeks, a target of 319 participants should be randomised per group, 638 in total.

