### Data collection, management and analysis

#### Plans for assessment and collection of outcomes

Following consent, the baseline questionnaire will be completed prior to surgery in-person or remotely. Completion of the baseline questionnaire will require input from local site staff and participants. The questionnaire will include the SPADI and EQ-5D-5L validated questionnaires and demographic data. The SPADI has 13 items divided into 2 subscales: pain (5 items) and disability (8 items). The responses are indicated on a Visual Analogue Scale (0=no pain/no difficulty and 10=worst imaginable pain/so difficult it requires help). The items are summed and converted to a total score out of 100, a high score indicates greater pain and disability.^7^ The EQ-5D-5L is a generic measure of health-related quality of life. It provides a single index value for health status that can be used in a clinical or health economic evaluation.^14^ The EQ-5D-5L consists of questions relating to five health domains (mobility, self-care, usual activities, pain/discomfort and anxiety/depression) and respondents rate their degree of impairment using five response levels (no problems, slight, moderate, severe or extreme problems). The EQ-5D-5L is the National Institute for Health and Care Excellence’s preferred measure of health-related quality of life in adults.

Follow-up questionnaires, including SPADI, EQ-5D-5L, self-report questionnaire for healthcare resource use, time to return to usual activities (including work) and any AEs, will be completed at 12 weeks, 6 and 12 months after randomisation (+4 weeks visit window to allow for reminders). This process will be coordinated centrally by the DCTSU. Follow-up questionnaires will be available in paper or electronic format. At 12 months following surgery, participants will be asked to undergo an ultrasound scan.

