#### Plans to promote participant retention and complete follow-up

If participants do not complete their questionnaires at the expected timepoints, they will be contacted at 2 weeks and a minimum data collection (SPADI and AEs) will be attempted via telephone at 3 weeks.

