### Statistical methods

#### Primary and secondary outcome analysis

Primary analyses will be conducted according to the intention-to-treat analysis group. ANCOVA will be used to compare total SPADI scores between individualised EPDR versus standard rehabilitation at 12 weeks after randomisation, adjusting for baseline SPADI score.

Among other secondary analyses, time to return to usual activities (work and driving) will be analysed using Kaplan-Maier curves and log rank test. Logistic regression will be undertaken to test the association between treatment groups and re-tear at 12 months. Linear regression will be used to test the association between treatment groups and time out of the sling over 4 weeks. Repeated measures ANCOVA will be used to test if any treatment effect exists and has been maintained up to 12 months in terms of SPADI and EQ-5D-5L scores. ANCOVA will be used to compare total SPADI and EQ-5D-5L scores between the treatment groups at 6 and 12 months adjusting for baseline scores. Safety analysis will be undertaken based on the per-protocol analysis group. The presence of AEs/serious AEs and problems after surgery will be compared between the two groups at 12 weeks, 6 and 12 months using χ^2^ test.

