#### Definition of analysis population relating to protocol non-adherence and any statistical method to handle missing data

Per-protocol analysis will consider patients with time out of the sling of 222.6 hours or more over 4 weeks compared with those with time out of the sling less than 222.6 hours base on the cut-off values from the RaCeR pilot.^6^ Missing values in the diary will not be included in the analysis.

Complete-cases analysis will be undertaken as part of the primary endpoint analyses, where cases with missing values or those completed outside the 4 weeks window will be excluded in each analysis. If substantial missing data (>10% and <20%) are observed in SPADI at 12 weeks or a key prognostic covariate for the primary analysis, then multiple imputation using chained equations will be applied. Complete-cases analysis will be undertaken for the secondary study outcomes.

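### Multiple imputation for the primary endpoint is prescribed only between 10% and 20% missing, so at 20% or more the only stated method is complete-case analysis

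*Protocol article*

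**What the plan says.** Under the statistical methods, the article states "Primary analyses will be conducted according to the intention-to-treat analysis group", and "ANCOVA will be used to compare total SPADI scores between individualised EPDR versus standard rehabilitation at 12 weeks after randomisation", with adjustment for baseline SPADI.

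The section on analysis populations and missing data makes complete-case analysis part of the primary endpoint analyses and adds that "cases with missing values or those completed outside the 4 weeks window will be excluded in each analysis". The condition for imputation follows: "If substantial missing data (>10% and <20%) are observed in SPADI at 12 weeks", or in a key prognostic covariate, "then multiple imputation using chained equations will be applied". Nothing is said about 20% or more. The text also leaves open whether imputation replaces the complete-case result or stands beside it, and whether an excluded late score counts as missing for the trigger. The secondary outcomes are to be analysed on complete cases.

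On data collection, the article allows a "4 weeks visit window to allow for reminders". For participants who have not responded, "they will be contacted at 2 weeks and a minimum data collection (SPADI and AEs) will be attempted via telephone at 3 weeks". The sample size section reaches its target after "adjusting for 10% non-response of SPADI questionnaire at 12 weeks".

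**The concern.** A rule for missing data should give at least as much protection when more is missing. This one gives less: imputation begins just above 10% and ends at 20%. The upper limit is written into the rule, so it is not a detail left to a later document. A statistical analysis plan would have to override it or extend it.

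No other stated analysis fills the gap. The 6- and 12-month SPADI comparisons are secondary and use complete cases, and the article describes no analysis for missingness that depends on the unseen score.

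Nobody is blinded and SPADI is self-reported. The recruitment section also expects some participants to find their allocation hard to accept because of perceived risks of EPDR. It is therefore plausible that response differs by arm and by how recovery is going. If 20% or more is missing, the stated plan offers nothing against which to test the complete-case result, and a method chosen at that point would be chosen after the extent of the missing data was known.

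**Working it through.** **1. Reproduce the plan's sample size.** Inputs from the sample size section: difference 8, SD 30, power 90%, significance level 5% (taken as two-sided, which reproduces the figure), r = 0.2, non-response 10%.

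- t-test: 296.5, rounded up to 297 per group (594 in total).
- ANCOVA: 297 × (1 − 0.2²) + 1 = 297 × 0.96 + 1 = 286.1, rounded up to 287 per group (574).
- Non-response: 287 / 0.90 = 318.9, rounded up to 319 per group (638).

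All three figures agree with the article.

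**2. Put the imputation band into participants.** 10% of 638 is 63.8 and 20% is 127.6.

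| Missing 12-week SPADI | Share of 638 | Stated method |
|---|---|---|
| up to 63 | up to 9.9% | complete cases |
| 64 to 127 | 10.03% to 19.9% | imputation triggered |
| 128 or more | 20.1% or more | complete cases; nothing else stated |

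The planned loss is 638 − 574 = 64 (10.03%), so the band starts where the design assumption ends. One further missing score, from 127 to 128, takes the imputation away.

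**3. Is this a power problem?** Complete-case power for 8 points by the noncentral t distribution, with residual SD 30 × √0.96 = 29.39, is 90.2% at 574 analysed, 86.6% at 510 (20% missing) and 84.4% at 478 (25% missing). The loss is modest and comes from non-response, not from the upper bound. Baseline SPADI explains r² = 4% of the outcome variance, so imputing from baseline would restore almost none of it.

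**4. Size of a possible bias.** The documents give no figure for how non-responders differ, so the shifts here are assumptions. Let m be the fraction missing in an arm and s the amount by which its non-responders score worse than its responders. The arm's full mean is the responder mean plus m × s.

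- Shift in the EPDR arm only: complete cases overstate the benefit by m × s.

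| m | s = 5 | s = 10 |
|---|---|---|
| 10% | 0.5 | 1.0 |
| 20% | 1.0 | 2.0 |
| 30% | 1.5 | 3.0 |

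- Same shift in both arms, equal missingness: the bias is zero.
- Same shift in both arms, unequal missingness: the bias is s times the difference in fractions. With 20% missing in EPDR, 30% in standard care and s = 10, the benefit is understated by (0.30 − 0.20) × 10 = 1.0 point.

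The direction and size are therefore unknown in advance. Against a target of 8 points, the plausible range is enough to need a planned analysis.

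**The case against.** The strongest reply is that the article is silent at 20% or more and does not forbid further analysis. It condenses a fuller protocol, and the statistical analysis plan is not shown. A reader might infer that the trial will certainly report nothing beyond complete cases. The documents do not support that. They support only that complete-case analysis is the one method stated there, under a rule whose upper limit is explicit and unexplained.

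Second, complete-case ANCOVA is unbiased if missingness depends only on arm and baseline SPADI, and standard imputation itself assumes missing at random. This stands. Deleting the limit alone would not deal with informative missingness, so a sensitivity analysis has to accompany it.

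Third, three stronger readings are tempting, and none holds.

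- *The cap costs power.* The figures in step 3 measure non-response; deleting the cap would change them little.
- *The analysis is not intention-to-treat.* Nothing has participants analysed outside their allocated arm. The exclusions make the set incomplete, which is a narrower point.
- *The window wrongly discards data and the sample size ignores this.* The window defines a 12-week endpoint and has a stated purpose, and both the reminder and the telephone collection fall inside it. The number of late returns is not given, and the 10% allowance can fairly be read as no usable response at that time point. Moving late scores into the primary analysis would blur a hypothesis set specifically at 12 weeks.

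**Conclusion.** The concern holds for the upper bound. As written, the rule withdraws imputation at 128 or more missing of 638 and states nothing in its place. What is at stake is bias: 1.0 to 2.0 points at 20% missing and 1.5 to 3.0 at 30%, if EPDR non-responders alone are 5 to 10 points worse. It is zero if the shift and the missingness are the same in both arms. These shifts are assumed. The thresholds of 127 and 128 depend only on the article's figures and on the target of 638 being randomised. If fewer than 20% of scores are missing, the upper bound never comes into play. The sample size is unaffected.

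**What to change.** - Delete the upper bound, so that multiple imputation applies whenever more than 10% is missing. Include auxiliary variables already collected, such as 6- and 12-month SPADI, tear size and site. State whether the imputed result replaces or supplements the complete-case one.
- Add a delta-based sensitivity analysis, with the shift allowed to differ by arm, because imputation alone assumes missing at random.
- Keep the 12-week endpoint with its 4-week window for the primary analysis. State that an out-of-window SPADI counts as missing for the 10% trigger, and add a sensitivity analysis that includes SPADI returned late.

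The cost is a few lines of wording and a little more analysis work, with no change to the sample size. The wording should be settled before outcomes are compared by arm.

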#### Economic analysis

The perspective for both within-trial and model-based economic analyses will be that of the NHS and personal social services.^15^ The economic analysis has three phases:

Development of a conceptual cost-effectiveness model structure: an initial conceptual cost-effectiveness model structure will be developed to estimate the long-term costs and quality-adjusted life-year of EPDR and standard rehabilitation.Within-trial cost-consequences analysis: health benefits will be quantified for changes in health-related quality of life, measured by the EQ-5D-5L. Healthcare resource use and costs observed during the trial period will be reported for each treatment group. Outcomes measured during the 12-month study period will be left undiscounted.Model-based economic analysis: The long-term costs and health outcomes of EPDR and standard rehabilitation will be modelled for their impact on clinically relevant events (eg, re-tear, reoperation), updating the state-transition model developed using the RaCeR pilot with parameters derived from data collected in RaCeR 2 and (where relevant) the published literature. Long-term predicted outcomes will be discounted at 3.5% per annum.^15^ The health economic analysis plan will be developed and finalised before analysis commenced and is anticipated to be disseminated in a separate publication.

#### Plans to give access to the full protocol, participant-level data and statistical code

The full protocol is available at https://www.fundingawards.nihr.ac.uk/award/NIHR133874. In the first instance, further requests for data can be made via the chief investigator (CL).

### Oversight and monitoring

#### Composition of the coordinating centre and TSC

The chief investigator (CL) is responsible for the conduct of the trial and will be supported by the TMG. The TMG oversees all day-to-day aspects of trial management and delivery. The independent TSC monitors the trial progress and ensures that is it is being conducted according to the protocol and the applicable regulations. The TSC has an independent chair (statistician), and four other independent members including a health economist, physiotherapist, surgeon and two PPI representatives as well as the chief investigator (non-independent). The TSC will meet annually. The chief investigator, associate investigator, statistician and trial manager will attend the TSC meetings and report on trial progress.

#### Composition of the data monitoring committee, its role and reporting structure

Given the nature of RaCeR 2, a separate data monitoring committee will not be convened and the TSC will take on the data monitoring role, as agreed by the funder.

#### AE reporting and harms

Number and nature of AEs at 12 weeks, 6 and 12 months will be measured via self-report questionnaire and clinician report. AEs might include an increase in shoulder pain requiring additional care, for example, prescribed medication or injection; infection up to 12 weeks postsurgery; other shoulder disorders, for example, stiffness; rotator cuff re-rupture requiring additional care, for example, injection, physiotherapy or surgery.

#### Frequency and plans for auditing trial conduct

Audits will be conducted by the sponsor (University Hospitals of Derby and Burton NHS Foundation Trust) according to their audit plan; these may be central or site audits and may be trial or process-level audits.

#### Plans for communicating important protocol amendments to relevant parties

Substantial amendments will be submitted by the sponsor to relevant regulatory bodies (Research Ethics Committee and Health Research Authority) for review and approval. The amendments will only be implemented after approval and a favourable opinion has been obtained. Non-substantial amendments will be submitted to the Health Research Authority for their approval/acknowledgement.

## Ethics and dissemination

We were granted ethical approval by London-Stanmore Research Ethics Committee (23/LO/0195). We will disseminate findings from RaCeR 2 to stakeholders via peer-reviewed publications and presentations at national and international conferences. Our website (www.racer2study.co.uk) will serve as a hub to videos describing the trial results to support patient and clinical decision-making.

### Patient and public involvement

PPI was embedded throughout our RaCeR pilot.^6^ Our PPI group informed the choice of primary outcome, directed the timing of the intervention, the reporting of ultrasound scans and the follow-up data collection methods. They will continue to be actively involved in all stages of RaCeR 2, including development of patient-facing documents and the qualitative interview schedule for the QRI. We will work collaboratively to cocreate dissemination materials such as blogs and social media posts accessible to members of the public. The coauthor MF is a TMG member. Our PPI group holds regular meetings, facilitated by our PPI lead (MM).

## Discussion

RaCeR 2 will be the largest RCT in the world investigating rehabilitation after rotator cuff repair.^5^ The findings will inform national and international clinical practice. Our primary outcome assesses pain and disability. Our comprehensive dataset will assess other outcomes of interest to the clinical community, including rotator cuff repair integrity, and the comparative cost-effectiveness of individualised EPDR versus standard rehabilitation.

### Study status

The RaCeR 2 trial (protocol version 2.2, 14 April 2023) opened to recruitment on 1 June 2023 and is scheduled to remain open until 31 May 2025.
